### Interim analyses {21b}

No interim analysis is planned as (i) part of the objective of the study is to determine if the intervention is sustainable over 12 months, and (ii) we are interested in the longer-term effects of the intervention on anaemia, blood pressure and blood glucose and early changes detectable between the groups may not be sustained.

### Methods for additional analyses (e.g. subgroup analyses) {20b}

Subgroup analyses will be performed for women with GDM and HDP separately and with both conditions. The analysis of secondary outcomes will be performed on all women reaching the study endpoint. A structured observation of health worker performance will be performed on a subsample of 200 women from 10 intervention and control PHC facilities to assess fidelity to the study intervention.

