### Additional consent provisions for collection and use of participant data and biological specimens {26b}

This study does not involve the collection of biological specimens. As part of the consent form, participants will be asked if they agree for their data until that point to be included if they withdraw from the study. Participants will be asked permission for the research team to share relevant data with the international study team.

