		Comparison of participating PHCs to non-participating PHCs in the district (size, location, number of pregnant women per year, sociodemographic indicators)	Local records	Study end
**Implementation**	Level of adherence to programme delivery as intended, including extent to which elements are implemented and/or adapted. Cost of delivering the programme	Ethnological observation to determine fidelity to SHP intervention delivery at different timepoints throughout the programme and different study visits	Interviews and FGDs	12 months and study end
		Proportion of intervention elements delivered as intended as measured by a checklist of essential elements	Checklists; Interviews and FGDs	12 months and study end
		Extent and number of adaptations to original protocol (fieldnotes, protocol amendments, app changes, additional trainings)	Checklists; Interviews and FGDs	Study end
		Cost of programme delivery (cost of intervention, training, materials, time-based activity costing)	Costing proforma	Study end
**Maintenance**	The degree to which the programme is sustained to the end of the trial (at the setting level) and to which the effects of the programme are maintained (at the individual level)	Level of intent to continue programme delivery (setting) as determined by in depth interviews with key stakeholders (PHC leads, other policy makers/local leaders) and Likert scale to community health workers and PHC doctors	Surveys; Interviews	12 months and study end
		Number of health workers trained to use the intervention Number of health workers who continue to use the intervention to study end Reasons for health worker drop outs	Intervention group only: SHP app, interviews	Study end

*Reach*: The absolute number, proportion and representativeness of individuals that participated in the trial (both arms), and the intervention compared to the total population of pregnant women in the setting.
*Effectiveness*: The impact of the intervention on clinical outcomes (described above); quality of life, measured using the EQ5D tool [34]; and economic outcomes (health expenses incurred during pregnancy, at the time of birth and in the postnatal first year, and incremental economic costs).
*Adoption*: The absolute number, proportion and representativeness of health care workers who participated in the study compared to all health workers in the study locations. Qualitative work will explore reasons for non-participation or drop-out.

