*Follow-up after anaemia, GDM or HDP condition*: We will compare how many women with anaemia undergo a haemogloblin test; how many women after HDP or GDM undergo BP measurement, and how many women after GDM undergo a glucose assessment (fasting or random capillary glucose, OGTT or HbA1c) within 6 weeks and 6 months and 12 months after birth.(4)Women’s wellbeing, mental health, lactation practice
*Wellbeing*: The impact of the intervention on women’s general wellbeing, mental health. We will use locally validated mental health and wellbeing tools (EQ-5D-3L, PHQ9 and GAD7 [35]) to compare changes between baseline and at 12 months.
*Lactation*: is one of the few interventions for which evidence supports a positive impact on maternal and newborn long-term health following a high-risk pregnancy, specifically one affected by GDM [36]. We will assess whether the additional support provided through the intervention can improve lactation practice using WHO Infant and Young Child Feeding indicators [37].

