### Participant timeline {13}

PHCs will be recruited and randomised before individual participant recruitment commences. After randomisation, ASHAs in the intervention clusters will attend the education programme to receive training on the clinical conditions, use of the point-of-care devices and SMARThealth Pregnancy app. Individual participants will be approached by their ASHA worker to participate after 12 weeks’ gestation. If they consent to participate in the study, a study team member will complete a baseline assessment, which includes questionnaires, blood pressure and haemoglobin measurement. A study team member will perform a mid-point assessment between 9 and 12 weeks after birth to capture events and healthcare utilisation including out-of-pocket costs around the time of birth. A study team member will conduct the final study visit 9–12 months after delivery, which will involve completing questionnaires, and measuring haemoglobin and blood pressure (Table 2).

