## Data collection and management

### Plans for assessment and collection of outcomes {18a}

Independent, GCP-certified, trained, study team members will be involved in data collection at each stage. Data collection will occur on three occasions at both the intervention and control sites: baseline (after 12 weeks’ gestation), 9–12 weeks and then 9–12 months post-birth. All data will be captured on tablet computers using the SMARTHhealth app adapted for the clinical research forms (CRFs). Data will be de-identified, saved and stored on a secure server at the George Institute of Global Health, India. Strategies to ensure data quality include using published, validated questionnaires and the CRFs developed and user tested in the SMART Health Pregnancy pilot study. The field team supervisor will check approximately 10% of all CRFs for accuracy against source data or by direct interview with participants.

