### Plans to promote participant retention and complete follow-up {18b}

Community education events will be held at intervention and control sites to promote the study and awareness of women’s health, anaemia, cardiovascular disease and diabetes. Refreshments and transportation costs will be provided to women at the baseline and annual study assessments.

ASHAs and PCPs will receive a small payment per participant to compensate for the time spent on the study. For women who move away from the study sites during their follow-up period, information on pregnancy complications and outcomes will be collected by phone where possible.

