### Confidentiality {27}

Throughout the study, all efforts will be made to maintain participant confidentiality. Each subject enrolled in the project will have a unique identifier (ID) of six digits. The first digits denote the study state (00 = Telangana, 01 = Haryana). The final four digits will denote the participant’s unique number, e.g. 00–0001 will be in Telangana and will be the first participant screened for both sites; 01–0002 will be in Haryana and will be the second participant screened for both sites. Participants who are screened but do not give consent or withdraw from the study will also receive a study ID to calculate intervention reach. Tablet computers used for data collection as part of the intervention and for the study assessments will be password protected with multifactor authentication. They will be used only by authorised users and stored in a secure location when not in use. Local data stored on mobile devices will be deleted daily following online database synchronisation. Participant-identifiable data will be collected in a separate database to the research data set and linked using a unique identifier (see above for details). This information will be held only for the study duration to enable follow-up by the study team.

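### Restricting secondary analyses to women who reach the study endpoint drops birth-period data already recorded for women who leave later

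*Protocol article*

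**What the plan says.** The analysis set for secondary outcomes is fixed in one sentence of *Methods for additional analyses {20b}*: "The analysis of secondary outcomes will be performed on all women reaching the study endpoint". The term for the endpoint is not defined further, and no outcome or time window is exempted.

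Other sections describe data that exist before the final visit:

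- *Plans for assessment and collection of outcomes {18a}* sets three collection occasions in both arms: "baseline (after 12 weeks’ gestation), 9–12 weeks and then 9–12 months post-birth".
- *Participant timeline {13}* gives the purpose of the middle visit as "to capture events and healthcare utilisation including out-of-pocket costs around the time of birth".
- *Secondary outcomes*, under Effectiveness, lists economic outcomes that include "health expenses incurred during pregnancy, at the time of birth and in the postnatal first year".
- *Secondary outcomes*, under clinical service delivery indicators, counts tests after anaemia, GDM or HDP "within 6 weeks and 6 months and 12 months after birth".
- *Additional consent provisions {26b}* says that "participants will be asked if they agree for their data until that point to be included if they withdraw from the study".

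The only missing-data provision, in {20c}, is multiple imputation for the primary outcome.

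**The concern.** For haemoglobin at 12 months, a woman without an endline visit has no value, so restricting to endline attenders discards nothing already known. The position differs for an outcome that is complete, and possibly recorded, months earlier. Excluding a woman from a birth-cost comparison because she left at seven months conditions the analysis on something that happened after randomisation and after the outcome itself.

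That matters more here than in a blinded trial. Participants, providers and assessors all know the allocation ({17a}). Intervention women may have up to seven programme visits (Table 1), while comparison women have only the study assessments beyond usual care. Staying to the end could therefore depend on arm and on engagement with care, and engagement is close to what the utilisation and testing outcomes measure. Some precision is also lost for no gain.

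**Working it through.** **1. The plan's own sample size.** Inputs from *Sample size {14}*: 53% v 44%, power 80%, 30 clusters (15 per arm), ICC 0.02, loss 20%. Two-sided alpha of 0.05 is assumed from the threshold in {20a}.

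- Per arm under individual randomisation: n = (1.96 + 0.84)² × (0.53×0.47 + 0.44×0.56) / 0.09² = 480.1 (computed with unrounded normal quantiles).
- Women per cluster: m = n(1 − ICC)/(15 − n×ICC) = 480.1×0.98/(15 − 9.60) = 87.2, against the stated 86. Power at 86 is 79.6%.
- Inflation: 86/0.80 = 107.5, so 108. Then 108 × 30 = 3240.

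The stated figures reproduce closely enough to build on.

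**2. Which outcomes the rule touches.**

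| Outcome | Known before endline? | Affected? |
|---|---|---|
| Costs and utilisation around birth | Yes, at the 9–12 week visit | Yes |
| Tests within 6 weeks | Window closes before that visit, but recording there is not confirmed | If recorded |
| Tests within 6 months | No both-arm study visit between 12 weeks and 9 months | Only if recorded from another source |
| Haemoglobin, OGTT, BP, wellbeing at about 12 months; infant feeding (Endline CRF) | No | No |
| Quality-of-care score; full first-year expenses | Not complete until 12 months | No complete value to lose |
| Reach; setting-level measures | Not tied to a woman's endline visit | No |

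**3. How many women.** At 20% loss, 0.20 × 3240 = 648 women do not reach endline and 2592 do. For costs and utilisation, 648 is a ceiling, because some will leave before the 9–12 week visit. The protocol does not say when losses fall. If 25%, 50% or 75% of leavers have earlier data (assumption), the counts are 162, 324 or 486.

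The testing outcomes apply only to women with the condition. At the 50% national anaemia figure for pregnancy quoted in {14}, the ceiling for haemoglobin tests is 0.50 × 648 = 324. For a condition affecting 10% to one sixth of women (assumption), it is about 65 to 108.

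**4. Precision.** Effective n per arm = 15m / [1 + (m − 1) × 0.02]. The ICC is the anaemia value, assumed for other outcomes.

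- Endline attenders only: m = 2592/30 = 86.4, giving 1296/2.708 = 478.6.
- All 648 added: m = 108, giving 1620/3.14 = 515.9, a gain of 7.8%.
- With 25%, 50% or 75% added: gains of 2.2%, 4.2% and 6.1%.
- In a subgroup of 10% of women: m rises from 8.64 to 10.8, and effective n from 112.4 to 135.5, a gain of 20%. At one sixth the gain is 18%. Both are ceilings.

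**5. Bias.** Let r be the true rate of a binary early outcome, L the share of women with that outcome who later leave, and g the gap between stayers and leavers. The rate among stayers is r + L×g, so the arm difference shifts by L×g (intervention) minus L×g (comparison). The values below are illustrations; none comes from the protocol.

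| L: intervention / comparison | g: intervention / comparison | Shift, points |
|---|---|---|
| 20% / 20% | 20 / 20 | 4 − 4 = 0 |
| 20% / 20% | 10 / 20 | 2 − 4 = −2 |
| 20% / 20% | 0 / 20 | 0 − 4 = −4 |
| 8% / 12% | 20 / 20 | 1.6 − 2.4 = −0.8 |

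Swapping the arms reverses the sign.

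**The case against.** A reader might infer that every secondary outcome is damaged. The protocol does not support that. Most woman-level secondary outcomes exist only at endline, adoption and maintenance measures sit largely at facility or health-worker level, and Reach explicitly keeps women who leave: "Participants who are screened but do not give consent or withdraw from the study will also receive a study ID to calculate intervention reach".

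A reader might also infer that a known 6-week test result is being thrown away. That is not established. Table 1 gives the Endline CRF as the source for blood pressure and glucose follow-up. The description of the 9–12 week visit does not mention these tests, although utilisation could cover them, and the content of Table 2 is not visible in the text reviewed. Nor do the calls to women who move add a lost outcome: "information on pregnancy complications and outcomes will be collected by phone where possible" describes data that are not themselves a listed secondary outcome, though they may bear on who counts as having had GDM or HDP.

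Third, bias is possible but not shown. The *Discussion* reports equal retention across arms in the pilot. That stands as evidence, but the pilot had 200 women at four sites, and equal rates do not show that the same kinds of women stayed.

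Finally, the sentence is loosely worded. It follows one about GDM and HDP subgroups and may mean only that all women, not just those subgroups, are analysed; the endpoint might include women followed by phone; and a detailed SAP is promised. Outcome-specific denominators could properly be left to that SAP. But the protocol did not leave the set open: it stated one, and as stated it fits the early outcomes badly. The consent provision for data before withdrawal suggests that the investigators intend to use such data, which is a reason to correct the sentence.

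**Conclusion.** The point holds for woman-level outcomes whose window closes before the 9–12 month visit. It is clear for costs and utilisation around birth, and conditional for 6-week or 6-month tests, which are affected only where recorded before endline. For these, the stated set drops recorded data and selects on a later event in an unblinded trial, and the imputation provision does not repair it because it covers the primary outcome alone.

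The size is modest. At most 648 of 3240 women could be excluded from the cost and utilisation outcomes, and fewer from the condition-specific tests. The gain in effective sample size from including them is at most about 8% overall, and could reach 18–20% in small condition subgroups under the assumed prevalences. These figures rest on the planned 20% loss, an ICC of 0.02 carried over from anaemia, and every leaver having usable earlier data. The size and direction of any bias cannot be derived from the protocol, and it could be zero. The sentence should be corrected before unblinding; the primary analysis is not touched by this point.

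**What to change.** Replace the sentence in {20b}, or override it in the SAP, with:

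> Each woman-level secondary outcome will be analysed in all enrolled women, by PHC of enrolment, with that outcome recorded for its own time window, whether or not they attended the final visit, including data obtained before withdrawal where consent allows.

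Keep the endline-attender set as a sensitivity analysis. It would also help to state whether tests within 6 weeks are recorded at the 9–12 week visit, since that decides whether the change affects them.

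The change needs no new data. Its cost is that denominators differ between timepoints and must be shown in the tables. It remains an available-case analysis: it removes selection on events after the outcome window but not selection on earlier loss, and it adds few or no women for the 12-month outcomes.

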### Methods in analysis to handle protocol non-adherence and any statistical methods to handle missing data {20c}

The primary analysis population will include all participants with endline clinical assessment and haemoglobin measurement recorded. An intention to treat population will be defined as those participants who received at least one assessment during pregnancy and one after birth who also have a complete endline assessment. In case of substantial missing primary outcome data, sensitivity analyses based on multiple imputations will be performed.

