### Strategies to improve adherence to interventions {11c}

Study staff will support ASHAs by attending visits (with participant permission) and providing support for using the technology until the ASHA feels confident of performing assessments independently. Periodic quality control visits will be made to observe the intervention delivered by ASHAs and assessed by the study team. Every 6 months, the study team will conduct a 1-day refresher training session for the ASHAs.

Compliance with the intervention visits will be monitored centrally by tracking the visits recorded in the SMARThealth Pregnancy app. If trends of non-engagement across multiple participants from the same ASHA worker or PHC are noted, the study team will arrange a site visit.

For some women in India, it is traditional to move back to their mother’s village for the baby’s birth and stay there for up to 6 months. If the mother’s village is another intervention site, then visits will be transferred to the ASHA in the mother’s village, if it is part of the SMARThealth Pregnancy intervention. If the village is not an intervention site or is a EUC site, then visits will be replaced with phone calls, resuming face-to-face visits when the woman returns to her original village. Phone call follow-up was demonstrated to be acceptable and feasible for ASHA workers and women in the pilot study following COVID-19 disruptions.

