## Statistical methods

### Statistical methods for primary and secondary outcomes {20a}

The primary analysis will be by intention to treat conducted at the participant level, using either random-effects models or generalised estimating equations adjusted for PHC clustering. We used a matched-pair design to balance cluster characteristics prior to randomisation, as recommended for community-based trials with a limited number of clusters [40]. Given the relatively small number of clusters, the analysis will not adjust for matching since this has been shown to provide unbiased estimates of the randomised intervention effect [41] and provide similar power to a matched analysis [40]. An unmatched analysis has the advantage that it can easily be conducted using participant-level data whilst allowing estimation of the intra-class correlation coefficient.

The final analysis is anticipated to occur 36 months after recruitment of the first participant. For the groups to be declared significantly different, the *P* value for the primary outcome must be ≤ 0.05. We will report the point estimate and confidence interval and present an assessment of the clinical relevance of our findings.

Baseline data will be presented for both groups. Continuous variables will be assessed for distribution, with appropriate statistical transformation (e.g. log or cubic splines) to correct for non-normality. Subgroup analyses will be performed by study location (Telangana or Haryana) to explore the effects of contextual factors on outcomes of interest. A detailed statistical analysis plan will be developed and publicly available before unblinding.

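### The set named intention to treat depends on attendance after randomisation, and it differs from the named primary analysis population, so the ITT label is wrong and the primary set is unclear

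*Protocol article*

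**What the plan says.** Section {20a} of the protocol article sets the basis of the main comparison: "The primary analysis will be by intention to treat conducted at the participant level".

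Section {20c} describes two sets of women.

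- The first is the primary set: "The primary analysis population will include all participants with endline clinical assessment and haemoglobin measurement recorded". It places no condition on earlier visits.
- The second carries the intention-to-treat name: "An intention to treat population will be defined as those participants who received at least one assessment during pregnancy and one after birth", restricted further to those "who also have a complete endline assessment".

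Section {20c} gives the second set no role beyond its name. On missing outcomes it adds: "In case of substantial missing primary outcome data, sensitivity analyses based on multiple imputations will be performed".

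Three other places bear on how the second set would work.

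- Section {18a}: "Data collection will occur on three occasions at both the intervention and control sites". These are a baseline in pregnancy, a visit at 9–12 weeks and a visit at 9–12 months after birth.
- Section {13} calls the middle one a "mid-point assessment between 9 and 12 weeks after birth". It also says that the final visit comprises questionnaires as well as haemoglobin and blood pressure.
- Section {11c} notes that some women go to their mother's village for the birth and "stay there for up to 6 months".

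**The concern.** Intention to treat means that women are analysed in the group to which their PHC was allocated, whatever their later attendance. PHCs are randomised before any woman is recruited (sections {13} and {16b}). Every condition of the set that {20c} calls intention to treat is therefore met or missed after randomisation. A set filtered in this way should not carry that name, least of all in a trial whose intervention aims to increase contact after birth.

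The label also creates a conflict. Section {20a} points to intention to treat for the primary result. Section {20c} gives the primary result to one population and the intention-to-treat name to a narrower one. Two analysts following the article could report different primary results, and one of those could be presented as intention to treat when it is not. If the narrower set were used, and if the excluded women differed between arms in number or in anaemia risk, the comparison would lose the protection of randomisation.

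**Working it through.** **1. The two sets side by side**

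| Condition | Primary analysis population ({20c}) | ITT population ({20c}) |
|---|---|---|
| Assessment in pregnancy | not required | required |
| Assessment after birth | not required beyond endline | required |
| Endline | clinical assessment and haemoglobin recorded | complete assessment |

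The second set is no wider than the first, and on the stricter reading it is narrower. The usual order is the reverse.

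**2. Who could fall out**

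- *Pregnancy condition.* Baseline is itself an assessment in pregnancy and follows consent ({13}), so this condition excludes almost nobody.
- *After-birth condition.* The study has only two assessments after birth, at 9–12 weeks and at endline. The word also in {20c} suggests that the after-birth assessment is separate from endline. On that reading the 9–12 week visit becomes mandatory. A woman who missed it, for example while at her mother's village, is dropped even with an endline haemoglobin. If endline counts for both conditions, nobody is lost here.
- *Complete endline.* Endline includes questionnaires. If complete covers these, a woman with haemoglobin recorded and a questionnaire missing is dropped.

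**3. The plan's own sample size**

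Inputs from section {14}: 53% vs 44%, ICC 0.02, 30 clusters (15 per arm), 86 women per cluster, 80% power. Two-sided 0.05 is assumed, because {20a} does not state sidedness.

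- Design effect = 1 + (86 − 1) × 0.02 = 2.70.
- Effective n per arm = 15 × 86 / 2.70 = 477.8.
- Normal-approximation power = 79.6%, which matches the stated 80%.
- Enrolment after 20% loss: 86 / 0.80 = 107.5, rounded up to 108; 108 × 30 = 3240, as stated.

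The sample size is not in dispute. The allowance for loss covers women without an endline. It does not cover further removal of women who have one.

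**4. Illustration of bias (assumed rates)**

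Take no true effect and 53% anaemia in both arms. Let q be the share of an arm's endline women who are excluded, and assume that 63% of the excluded are anaemic. The prevalence left is (0.53 − 0.63q) / (1 − q).

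| Excluded, control / intervention | Control | Intervention | False difference |
|---|---|---|---|
| 15% / 5% | 0.4355 / 0.85 = 51.2% | 0.4985 / 0.95 = 52.5% | 1.2 points |
| 25% / 10% | 0.3725 / 0.75 = 49.7% | 0.4670 / 0.90 = 51.9% | 2.2 points |

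Over a wider grid (5% excluded in intervention, 10–20% in control, 60–70% of the excluded anaemic), the difference runs from 0.4 to 3.4 points. In all of these cases it goes against the intervention, and it would reverse if the pattern reversed. It is zero if the excluded have 53% prevalence. It is also zero if both arms lose the same share with the same prevalence.

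**5. Power under the same assumed exclusions**

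This uses a noncentral t with 28 df (30 clusters − 2), 53% vs 44%, and 86(1 − q) women per cluster in each arm.

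- No extra exclusion: 77.0%.
- 15% / 5% (73.1 and 81.7 women per cluster): 75.3%.
- 25% / 10% (64.5 and 77.4 women per cluster): 73.7%.

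The loss is about 2 to 3 points.

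**The case against.** The strongest reply is that {20c} does name a primary population, and that it is nearly the right one: it needs an endline and a haemoglobin value and nothing earlier. The phrase in {20a} can then be read as a principle, analysis by the PHC's allocation, which fits section {16c}. This stands in part. A reader might infer that the main comparison will be made in the attendance-based subset, but the article does not say so. The conflict remains, because {20c} goes on to attach the same term to a different set.

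A reader might also infer that women with a known outcome will certainly be dropped. The text does not establish that. Endline may count as the assessment after birth. Women who move away may be reached by phone ({18b}), although {20c} does not say whether a call counts as an assessment. The exclusion criteria for women describe the usual stay away as a few weeks, with six months the upper limit given in {11c}.

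A further tempting reading is that an assessment means a health worker's app visit. That cannot be intended, since it would leave the control arm of the set empty, and {18a} describes data collection at both kinds of site.

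On size, nothing in the article supports the assumed exclusion rates or the 63%. Its only evidence on retention is the Discussion's report of equal recruitment and retention across groups in the pilot, which points away from a difference between arms. That evidence makes a large bias less likely, but it does not correct the label.

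Finally, it may look like a fault that imputation depends on missingness being substantial when 20% loss is already expected. The threshold and the imputation model are details that a protocol article commonly leaves to the SAP, and {20a} promises one before unblinding. This is no finding.

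**Conclusion.** The point holds as a wrong label and an internal conflict, and neither needs any assumption. Section {20a} makes the primary analysis intention to treat, while {20c} gives that name to a set selected on events after randomisation and gives the primary analysis to another set. Followed as written, a result could be reported as intention to treat when it is not.

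The loss of women with a recorded outcome is possible, not established. It depends on reading the after-birth assessment as separate from endline, or complete as including questionnaires. The illustrated bias of 1.2 to 2.2 points and the power loss of 2 to 3 points rest wholly on assumed exclusion rates, and the bias also on an assumed prevalence among the excluded. They show scale only and do not predict what will happen. The labelling conflict should be settled before unblinding.

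**What to change.** State one primary set in {20a} and {20c}: all enrolled women, analysed by the allocation of their PHC, using every recorded endline haemoglobin regardless of other visits or questionnaire completeness. Reserve the term intention to treat for that set.

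Rename the set that requires an assessment in pregnancy, one after birth and a complete endline (per-protocol, for instance). Define what counts as an assessment, including whether a phone contact does, and give the set a supportive role only. Otherwise delete it.

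The handling of missing haemoglobin, including any threshold and the imputation model, can be left to the SAP.

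The cost is a change of wording and at most one supportive analysis. No new data are needed and the sample size does not change.
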